#### Power

Using the UK Biobank protein expression GWAS,^43^ the lead *cis* SNP for *PDCD1* (variant located at chr2:242801752 in human genome build 37 (hg37) with CG (A0) and C (A1) alleles) explained approximately 2.97% of the variation in circulating PD-1 expression level while the lead *cis* SNP for *CD274* (rs822341) explained approximately 4.17% of the variation in PD-L1 expression level.

Across all seven cancer types, there is an estimated power of 80% to detect HRs of at least ≥1.63 or ≤ 0.62 per unit decrease in normalised protein expression levels (alpha set to 5%) (table 3).

**Table 3 T3:** Estimated number of participants (N), death proportion, median survival, and HR per SD decrease detectable with 80% power for each cancer site

Cancer	N	Death proportion	Median survival (months)	HRs detectable at estimated 80% power	
				PD-1	PD-L1
Breast	93 869	0.083	64.8^71^	HR ≥ 1.21 HR ≤ 0.83	HR ≥ 1.17 HR ≤ 0.86
Colorectal	19 154	0.238	38.4^71^	HR ≥ 1.28 HR ≤ 0.78	HR ≥ 1.22 HR ≤ 0.82
Head and neck	10 196	0.331*	54.3^72^	HR ≥ 1.34 HR ≤ 0.75	HR ≥ 1.26 HR ≤ 0.79
Lung	8670	0.599*	3.6^71^	HR ≥ 1.27 HR ≤ 0.79	HR ≥ 1.21 HR ≤ 0.83
Melanoma	11 201	0.103	53.4^73^	HR ≥ 1.63 HR ≤ 0.62	HR ≥ 1.50 HR ≤ 0.67
Ovarian	3395	0.552*	30.1^74^	HR ≥ 1.48 HR ≤ 0.68	HR ≥ 1.37 HR ≤ 0.73
Prostate	24 023	0.146	62.4^71^	HR ≥ 1.33 HR ≤ 0.75	HR ≥ 1.26 HR ≤ 0.79

HRs per standard deviation (SD) decrease estimated to be detected at 80% power calculated with the survSNP R package^75^ (https://cran.r-project.org/web/packages/survSNP/index.html) using the combined estimated sample size and death proportion from each cancer survival genome-wide association study (GWAS) and the respective Genomics England cancer survival GWAS, median survival and assuming a false positive rate of 0.05. Death proportion was defined as the proportion of cancer cases who died due to all-cause or cancer-specific mortality. Transformation of protein level measurements into normalised protein expression (NPX) units on a log₂ scale have been described previously.^43^

*Death proportion due to all-cause mortality.

#### Positive controls

Positive control analyses investigate the association between the exposure of interest and an outcome which has already been observed to have a causal association with this exposure.^58^ This enables the reliability of the genetic instruments for such exposures to be validated.^59^ For these analyses, the positive control outcomes will be survival for cancers at sites which PD-1 or PD-L1 inhibitors have been approved for treatment by the MHRA (ie, breast, head and neck, colorectal, lung and melanoma cancer survival) (table 1). However, these analyses will be crude positive controls as these drugs are approved to treat highly specific patient populations (online supplemental table 1), whereas the cancer survival data have been generated from broader patient populations.

#### Instrument validation

Our main analyses assume that SNPs associated with circulating PD-1 or PD-L1 protein expression level in the general population will have similar effects on protein levels in cancer cases and biologically relevant tissues (defined as those tissues responsible for the therapeutic benefit of PD-1 or PD-L1 inhibition). However, as PD-1 expression is upregulated due to T cell activation and PD-L1 expression is induced by inflammation and carcinogenesis, SNP-protein effects may differ between the general population and cancer cases.^60 61^ Thus, we will compare the strength and direction of SNP-protein associations among cancer cases, participants without a cancer diagnosis and in samples broadly representative of the general population in UK Biobank.^62^ We will perform these analyses for UK Biobank cancer cases pooled across the seven cancer sites which our analyses focus on (n=3375), each of the seven cancer sites individually (table 4), and pooled across all cancer sites.^62^

**Table 4 T4:** Number of incident UK Biobank cancer cases with protein expression data available for each cancer site and corresponding International Classification of Diseases 10th revision (ICD-10) code

Cancer site	ICD-10 code	N
Breast	C50	780
Colorectal	C18-20	545
Head and neck	C00-C14, C32	124
Lung	C34	391
Malignant melanoma	C43	292
Ovary	C56	89
Prostate	C61	1154

Number of participants with each ICD-10 code obtained from Papier *et al* (2023).^62^

The genetic instruments proxying circulating PD-1 or PD-L1 protein concentration will be further validated by investigating the strength and direction of the SNP-protein associations in UK Biobank cancer cases who were diagnosed with cancer prior to blood collection (prevalent cases) and those diagnosed with cancer following blood collection (incident cases). We will also assess whether the associations between these genetic instruments and circulating PD-1 or PD-L1 level differ by patient time since diagnosis. These sensitivity analyses will enable assessment as to whether the associations between these genetic instruments and circulating PD-1 or PD-L1 level (and so their strength as genetic instruments) differs for patients with cancer over time.

Additionally, as PD-L1 is expressed by cells at a number of potentially biologically relevant tissues aside from blood, such as the tumour site, endothelial cells and sites of metastases,^60^ we will also investigate the association between the constructed genetic instruments and expression of the gene encoding PD-L1, *CD274,* in these tissues.

For each cancer site of interest, we will explore the strength and direction of association between these genetic instruments and *CD274* expression in tumour samples obtained from The Cancer Genome Atlas Program dataset (https://www.cancer.gov/tcga) (table 5) to validate the instruments’ strength in the biologically relevant target population and target tissue.

**Table 5 T5:** Estimated number of tissue samples with germline genotype and gene expression data (N) available from The Cancer Genome Atlas Program (TCGA) dataset (https://www.cancer.gov/tcga) for each cancer site

Cancer site	Study name	Study abbreviation	N
Breast	Breast invasive carcinoma	BRCA	770
Colorectal	Colon adenocarcinoma	COAD	298
	Rectum adenocarcinoma	READ	109
	Total	–	407
Head and neck	Head and neck squamous cell carcinoma	HNSC	366
Lung	Lung adenocarcinoma	LUAD	385
	Lung squamous cell carcinoma	LUSC	334
	Total	–	719
Melanoma	Skin cutaneous melanoma	SKCM	54
Ovarian	Ovarian serous cystadenocarcinoma	OV	211
Prostate	Prostate adenocarcinoma	PRAD	366

We will also investigate the strength and direction of these associations for each anatomical site using tissue sample data obtained from the Genotype-Tissue Expression database (https://www.gtexportal.org/home/) (table 6) and for immune cell populations obtained from Database of Immune Cell Expression, Expression quantitative trait loci and Epigenomics (DICE) (https://dice-database.org/). This will enable validation of the strength and direction of association of these instruments in the tissues of interest and further understanding of the background level of expression of this gene not specific to cancer biology.

**Table 6 T6:** Estimated sample sizes (N) available for measurements of gene expression in tissues at each anatomical site of interest obtained from the Genotype-Tissue Expression (GTEx) version 8 dataset (https://www.gtexportal.org/home/tissue/)

Tissue site	GTEx tissue name	N
Breast	Breast—mammary tissue	396
Colorectal	Colon—sigmoid	318
	Colon—transverse	368
	Total	686
Head and neck	Minor salivary gland	144
Lung	Lung	515
Melanoma	Skin—not sun exposed (suprapubic)	517
	Skin—sun exposed (lower leg)	605
Ovarian	Ovary	167
Prostate	Prostate	221

Furthermore, as T cell level and function are affected by interactions between PD-1 and PD-L1, we will investigate the strength and direction of association of these genetic instruments with white blood cell count and function in general population samples as well as UK Biobank cancer cases and cancer-free participants.^10 12 60 63^ This will serve as a positive control analysis, as we would expect that the genetic instruments proxying circulating PD-1 or PD-L1 levels will be associated with white blood cell metrics. Additionally, if the genetic instruments are associated with white blood cell metrics and cancer survival, this will provide evidence supporting a mechanism through which circulating PD-1 and PD-L1 level affects cancer survival mediated by white blood cells.

Overall, these validation analyses will enable assessment as to whether it is appropriate to assume that SNPs associated with circulating PD-1 or PD-L1 levels can also be used to proxy expression of these proteins at multiple anatomical sites in cancer cases and in biologically relevant tissues.

#### Sensitivity analyses

The main analyses will be repeated using genetic instruments constructed with more stringent thresholds: significance p value thresholds of < 5 × 10^−7^ and < 5 × 10^−8^, window sizes of 250 kb and 100 kb on either side of the gene of interest, and LD r^2^ thresholds of 0.2, 0.1 and 0.001. Although the primary analysis will only consider *cis* variants, *cis* and *trans* variants (> 500 kb from the gene of interest) will also be considered in secondary analyses. Instruments constructed from *cis* and *trans* variants will be selected based on p value and LD threshold (p < 5 × 10^−8^, r^2^ < 0.001) with reference to a random sample of 10 000 participants of European ancestry from the UK Biobank. Where instruments are constructed from two or more SNPs, the primary analysis will also be re-run iteratively excluding individual SNPs from instruments to investigate whether findings are driven by individual SNPs.^42^

Colocalisation analysis will be performed using Pair-Wise Conditional analysis and Colocalisation analysis (https://github.com/jwr-git/pwcoco) to investigate whether any significant MR results are biased due to LD between one variant causing a change in protein expression and another causing a change in cancer survival through an independent pathway.^4 55 64 65^

Pleiotropy will be investigated by conducting phenome-wide association studies to investigate whether the genetic instruments proxying PD-1 or PD-L1 expression are also associated with other phenotypes. This will be achieved using the IEU Open GWAS project (https://gwas.mrcieu.ac.uk/).^49 50^ The significance thresholds will be Bonferroni corrected for the number of traits looked up.^37 55^ Although these methods will not specifically investigate horizontal pleiotropy, they will assess the possible extent of either vertical pleiotropy or horizontal pleiotropy. Vertical pleiotropy occurs when there is a mediator in the pathway between the exposure and outcome and, in contrast to horizontal pleiotropy, does not violate MR assumptions.^38 42 51 64^

Index event bias (also known as collider bias) may occur in studies of cancer survival if the hypothesised causal factor being evaluated for disease prognosis (in this case, PD-1 or PD-L1) is also a risk factor for disease onset.^4 37 66^ If SNPs found to be significantly associated with cancer survival are also associated with risk of the same cancer type, methods including the SlopeHunter R package (https://github.com/Osmahmoud/SlopeHunter) will be used to evaluate and account for index event bias.^67 68^

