The interaction between PD-L1 on the surface of cancer cells and PD-1 on the surface of activated T cells suppresses further T cell activation.^10 20 21 28^ Therefore, PD-1 and PD-L1 inhibitors suppress this interaction and so support T cell activation during anti-cancer immune responses.^10 12^ While PD-1 is largely expressed on immune cells, PD-L1 is expressed on a wider variety of non-haematopoietic cells, including tumour cells.^29–32^ Although there is uncertainty over the prognostic value of blood-based measures, previous studies have found that higher circulating (ie, blood-based) PD-1 and PD-L1 levels are associated with poorer prognosis for patients diagnosed with cancer at different anatomical sites. For example, higher plasma soluble PD-1 and PD-L1 expression levels were associated with decreased progression-free survival for patients with advanced-stage high-grade serous ovarian cancer compared with those with lower PD-1 and PD-L1 expression.^33^ However, when accounting for other clinical factors in multivariable analyses, only soluble PD-L1 expression levels remained associated with progression-free survival for these patients.^33^ Higher circulating soluble PD-L1 expression was also associated with decreased overall and progression-free survival in a meta-analysis of patients with cancer at different anatomical sites, including non-small cell lung cancer and melanoma patients who had been treated with immunotherapy.^34^ In contrast, although low serum exosomal PD-L1 expression was associated with increased median overall survival for pancreatic ductal adenocarcinoma patients compared with those with high exosomal PD-L1 expression, there was little statistical evidence to support this observed difference.^35^ Therefore, even though the prognostic roles of circulating PD-1 and PD-L1 expression levels have not been fully determined, there is some evidence supporting an association between blood-based measures of these immune checkpoint proteins and cancer survival, and the mechanism of action of these drugs is mediated by T cells.^33–35^

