## Methods and analysis

### Exposures

Rather than investigating the efficacy of specific immune checkpoint inhibitor compounds, their on-target effects will be proxied using genetic instruments which represent decreased circulating levels of their protein targets, PD-1 and PD-L1. Since our primary instruments will be based on studies in blood, we anticipate that our analyses may not fully proxy the mechanism of PD-1 and PD-L1 inhibitors in all biologically relevant tissues, an issue we will address in instrument validation analyses (see below).

Single-nucleotide polymorphisms (SNPs) associated with circulating PD-1 or PD-L1 expression levels will be used to proxy expression of these proteins. These genetic instruments will be selected from a GWAS of circulating proteins in 54 219 participants of majority European ancestry in the UK Biobank cohort.^43^ Statistical analysis, imputation, quality control and protein expression quantification in this study have been described previously.^43^

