#### Genetic instrument selection

The UK Biobank protein expression GWAS summary statistics^43^ will be used to select SNPs associated with circulating PD-1 or PD-L1 concentration. The genomic regions of the genes encoding PD-1 (*PDCD1*, chr2:241849884–241858894 in human genome build 38 (hg38)) and PD-L1 (*CD274*, chr9:5450503-5470566 in hg38) will be used to define *cis* and *trans* genetic instruments based on different window sizes.

To minimise vulnerability to horizontal pleiotropy, only SNPs within and in proximity to the gene encoding the target protein, known as *cis* SNPs, will be included in genetic instrument sets for the main analyses.^51^
*Cis* instruments to proxy both proteins will be constructed in PLINK version 1.9^52 53^ using SNPs in or within 500 kilobases (kb) from *PDCD1* or *CD274* that are associated with expression of these proteins (p < 5×10^-6^) at linkage disequilibrium (LD) r^2^ < 0.30 (based on clumping with a random sample of 10 000 European participants from the UK Biobank).^5 51 54^

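### The secondary *cis*-plus-*trans* instruments do not exclude the other target's gene region, so a PD-L1 variant could enter the PD-1 instrument, or the reverse, if one passes the selection threshold

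*Protocol article*

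**What the plan says.** The main analyses use *cis* instruments only. The article gives the reason under Genetic instrument selection: "To minimise vulnerability to horizontal pleiotropy, only SNPs within and in proximity to the gene encoding the target protein, known as" *cis* SNPs, go into the main instrument sets. The same section locates the two genes: *PDCD1* (PD-1) at "chr2:241849884–241858894 in human genome build 38 (hg38") and *CD274* (PD-L1) at "chr9:5450503-5470566 in hg38".

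The Sensitivity analyses section then widens the set. *Trans* "variants (> 500 kb from the gene of interest) will also be considered in secondary analyses". Three conditions define membership. The first is distance from the gene of interest. The other two come in the next sentence, by which *cis* and *trans* "variants will be selected based on p value and LD threshold", with p < 5×10^-8 and r² < 0.001. Nothing there or elsewhere in the article treats the other target's gene region differently from the rest of the genome.

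**The concern.** The study instruments PD-1 and PD-L1 separately and aims to judge the repurposing potential of each. The two are a receptor and its ligand. The Introduction says: "The interaction between PD-L1 on the surface of cancer cells and PD-1 on the surface of activated T cells suppresses further T cell activation". A variant in one gene that also shifts the circulating level of the other protein is therefore biologically conceivable.

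Under the plan's own hypothesis, a *CD274* variant may act on survival through PD-L1. Placed in the PD-1 instrument, it may have a route to survival that does not run through PD-1. That is horizontal pleiotropy, which the Assumptions section says must be absent. Unlike ordinary *trans* pleiotropy, this route can be named in advance, because it is the study's other exposure.

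What is at stake is the target-specific reading of the secondary estimates. Table 1 shows why the distinction matters: colorectal cancer, head and neck cancer and melanoma have PD-1 approvals but no PD-L1 approvals.

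**Working it through.** The article gives no figure for the *trans* instruments, so there is none to reproduce. The check has a logical part and an illustration of size.

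**Logic.** *CD274* is on chromosome 9 and *PDCD1* on chromosome 2. Every variant in one gene's region is therefore more than 500 kb from the other gene and meets the distance condition. The r² < 0.001 condition does not remove it either, because LD between the two chromosomes is negligible. Only p < 5×10^-8 for the other protein stands between the variant and the instrument.

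**Inputs.**
- Exposure GWAS size, from Exposures: "GWAS of circulating proteins in 54 219 participants of majority European ancestry".
- Lead *cis* SNPs, from Power: the *PDCD1* SNP "explained approximately 2.97% of the variation in circulating PD-1 expression level"; the *CD274* SNP explains 4.17% for PD-L1.
- Events, from Table 2: ovarian 1873, breast 7769.
- PD-L1 HR 0.73, the detectable effect for ovarian cancer in Table 3, used here as an assumed true effect.
- Assumed, because the article does not report it: the share r of the recipient protein's variance explained by the other gene's lead SNP.

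**Entry threshold.** The two-sided 5×10^-8 limit corresponds to z² = 29.72. The smallest r that reaches it is about 29.72 / 54 219 = 0.00055 (0.055%). For the *CD274* lead SNP to reach this for PD-1, PD-1 must move by about √(0.00055 / 0.0417) = 0.115 SD per SD of PD-L1. In reverse, the figure is √(0.00055 / 0.0297) = 0.136.

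**Leakage.** Take one *cis* SNP and one cross-gene SNP, standardised genotypes, equal outcome standard errors, and inverse-variance weighting. The fraction of the other target's log HR that enters the estimate is

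√(r × R²_other) / (R²_own + r)

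| Estimate affected | r = 0.00055 | r = 0.002 |
|---|---|---|
| PD-1 (receives PD-L1) | 0.00478 / 0.03025 = 0.158 | 0.00913 / 0.0317 = 0.288 |
| PD-L1 (receives PD-1) | 0.00403 / 0.04225 = 0.095 | 0.00771 / 0.0437 = 0.176 |

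A stronger cross-association leaks more. At 0.5 SD of one protein per SD of the other, the fractions are 0.52 and 0.30. Below the entry threshold the SNP is generally not selected, and leakage by this route is essentially nil.

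**On the HR scale.** Suppose PD-L1 has HR 0.73, PD-1 has no effect, and the variant moves both proteins in the same direction. The PD-1 HR becomes exp(0.158 × ln 0.73) = 0.95 at entry and exp(0.288 × ln 0.73) = 0.91 at r = 0.002.

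**Against the noise.** The standard error is about 1/√(events × (R²_own + r)).
- Ovarian: 1/√(1873 × 0.03025) = 0.133 and 1/√(1873 × 0.0317) = 0.130. The results are HR 0.95 (95% CI 0.73 to 1.23), |z| = 0.37, and HR 0.91 (0.71 to 1.18), |z| = 0.70.
- Breast, with the same assumed HR: |z| = 0.76 and 1.42.

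**Would Cochran's Q see it?** The cross-gene SNP's own PD-1 ratio would be exp(ln 0.73 / 0.115) = 0.06 at entry. At r = 0.002 the slope is √(0.002 / 0.0417) = 0.219, and the ratio is exp(ln 0.73 / 0.219) = 0.24. The *PDCD1* SNP gives 1.00. With two SNPs and sampling error set aside, Q = events × R²_own × r / (R²_own + r) × (log ratio)². In ovarian cancer this is about 7.6 and 7.2 on 1 df (p about 0.006 and 0.007); in breast it is at least 30.

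**The case against.** The strongest reply has four parts.

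*Size.* The illustrated shift lies inside the noise, and Table 3 puts the detectable PD-1 HR at 0.68 for ovarian and 0.83 for breast cancer. This stands. A reader might infer that PD-L1 could make PD-1 look like a second effective target. The figures at and just above the threshold do not support that: the shift would rarely create a significant result on its own.

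*Planned checks.* Cochran's Q with visual comparison of SNPs, the phenome-wide look-up, and the test of the instruments against *CD274* expression could each expose such a variant. This stands in part. None has a stated rule for dropping a SNP, and iterative SNP exclusion is stated for the primary analysis only. Colocalisation would not help, since a single variant affecting both PD-1 level and survival would be expected to colocalise.

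*Vertical pleiotropy.* If a *CD274* variant acts on survival wholly through PD-1, it is a valid PD-1 instrument, and dropping it discards information. This is fair, and it argues for showing both estimates rather than only excluding. It does not close the gap, because the plan also instruments PD-L1 as an exposure in its own right.

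*Scope.* The analysis is secondary, the main analysis already uses *cis* SNPs to limit pleiotropy, and a condensed article may leave filters to a fuller plan. The first two parts stand. On the third, the article does state its selection rule, with distance, p and LD limits, and that rule as written admits the other target's region.

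**Conclusion.** The point holds as a minor, conditional gap. The stated rule allows one target's gene-region variants into the other target's *cis*-plus-*trans* instrument, and nothing in the article prevents or resolves it.

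Two stronger readings are not supported. The rule does not admit every variant beyond 500 kb, because p < 5×10^-8 and r² < 0.001 also apply. Nor does it follow that the two targets' estimates do contaminate each other: that needs a genome-wide significant cross-gene association, in each direction separately, and the article reports neither its presence nor its absence.

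If such a variant exists, the leak at and just above entry is about 0.16 to 0.29 of the PD-L1 log HR into PD-1 and 0.10 to 0.18 in reverse. These figures rest on a two-SNP instrument, an assumed r of 0.055% to 0.2%, and the intruding SNP acting on survival only through its own target. Further SNPs dilute the leak, and its sign depends on whether the variant moves both proteins the same way. The *cis*-only main estimates are unaffected in every case.

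**What to change.** Add to the Sensitivity analyses section: the *cis*-plus-*trans* instruments will be built without variants within 500 kb of the other target's gene (*CD274* for the PD-1 instrument, *PDCD1* for the PD-L1 instrument); the report will state whether any variant was removed; and where one was, the estimate with it included will also be shown.

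This takes one sentence and one filter. If no such variant exists, nothing changes. If one does, the loss of instrument strength is trivial near the threshold: the variant adds 0.055% to 0.2% of explained variance beside 2.97% or 4.17% from the lead *cis* SNP. Showing both estimates keeps the information if the variant proves to act through the intended target.

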### Mendelian randomisation

#### Assumptions

There are three key assumptions of MR: relevance, exchangeability and exclusion restriction.^39 42^ The relevance assumption states that the genetic instrument must be associated with the exposure of interest, for example, in this study the circulating levels of the drugs’ protein target.^36 42^ The second MR assumption, exchangeability, requires there are no common causes of the instrument and outcome.^36 42^ The final MR assumption, exclusion restriction, states that there must be no horizontal pleiotropy.^36 38–41 51^ Horizontal pleiotropy occurs when there are additional pathways between the instruments and outcome, independent of the exposure.^36 42 51^

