#### Estimator

Where the genetic instrument consists of one SNP, the Wald ratio will be used to assess the association between a protein instrumented by this SNP and cancer survival.^6 40 55^ Where a genetic instrument consists of two or more SNPs, the inverse-variance weighted method will instead be used to investigate the association between a protein instrumented by these SNPs and cancer survival.^6 40 55^ Any LD between SNPs included in an instrument will be accounted for in analysis using a SNP correlation matrix based on a random sample of 10 000 participants of European ancestry from the UK Biobank.^42 54 56^ Heterogeneity of MR results across independent SNPs included in the genetic instrument sets will be assessed using Cochran’s Q tests and MR results will be compared across each SNP in the instrument by visual inspection.^36 40 57^

The protein expression GWAS included age, age², sex, age–sex interaction terms, protein expression level measurement batch, UK Biobank centre, genotyping array, the first 20 principal components (PCs) of genetic ancestry, and duration between blood sample collection and protein expression measurement as covariates, in addition to preselection status of the participants for the replication cohort.^43^

Aside from the breast cancer GWAS which did not adjust for any covariates, the cancer site-specific GWAS were all adjusted for genetic PCs (although for different numbers of PCs).^44–48^ The colorectal cancer survival GWAS additionally adjusted for age at diagnosis, sex, genotyping platform and study where the data originated from.^45^ The head and neck cancer GWAS will be additionally adjusted for age, sex, stage at diagnosis (stratified as early or late stage) and cancer subtype. The lung cancer survival GWAS also adjusted for age and sex, and separated participants into early-stage (stage I–II), late-stage (stage III–IV) and all stage analyses (unpublished). The melanoma survival GWAS included age and sex as covariates in addition to genotyping batch for one cohort.^46^ For the ovarian cancer survival GWAS, the primary study, residual disease, tumour stage, histology, tumour grade and age were also adjusted for.^47^ The prostate cancer survival GWAS additionally included age, diagnostic prostate-specific antigen level and Gleason score as covariates.^48^

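### The secondary cis-plus-trans instruments get IVW as their only estimator, with no estimate that tolerates directional horizontal pleiotropy

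*Protocol article*

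**What the plan says.** All references are to the protocol article.

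- **Assumptions** sets the standard: "The final MR assumption, exclusion restriction, states that there must be no horizontal pleiotropy".
- **Genetic instrument selection** gives the reason for the main instrument: "To minimise vulnerability to horizontal pleiotropy, only SNPs within and in proximity to the gene encoding the target protein" are used in the main analyses.
- **Sensitivity analyses** then widens the instrument. Trans variants, defined as lying more than 500 kb "from the gene of interest) will also be considered in secondary analyses". Cis and trans "variants will be selected based on p value and LD threshold" (p < 5×10^-8, r² < 0.001). No pleiotropy filter and no change of estimator is attached.
- **Estimator** gives a two-part rule: the Wald ratio for a single SNP, and otherwise "Where a genetic instrument consists of two or more SNPs, the inverse-variance weighted method will instead be used to investigate the association". No other multi-SNP estimator appears in the article.
- **Checks listed.** Under Estimator: "Heterogeneity of MR results across independent SNPs included in the genetic instrument sets will be assessed using" Cochran's Q, with visual comparison across SNPs. Under Sensitivity analyses: leave-one-out, worded as "the primary analysis will also be re-run iteratively excluding individual SNPs from instruments"; colocalisation for significant MR results; and a phenome-wide look-up of the instruments, which the authors concede does not isolate horizontal pleiotropy.

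**The concern.** The main analysis guards against horizontal pleiotropy through its choice of variants. The cis-plus-trans analysis gives up that protection and puts nothing in its place at the estimation stage. IVW is consistent only if all variants are valid or their pleiotropic effects average to zero. If trans variants affect survival by routes that bypass PD-1 or PD-L1, mostly in one direction, the pooled estimate moves with them.

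What is at stake is how the cis-only and cis-plus-trans results are read together. The secondary analysis is there to test robustness. If the two differ, the plan offers no estimate that would help tell pleiotropy from chance or from the extra information in the trans SNPs. If they agree, no pleiotropy-tolerant estimate backs the agreement. The problem is easy to remedy: at r² < 0.001 the SNPs are close to independent, so standard robust estimators can be applied directly.

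**Working it through.** The article gives no figure for this analysis, so there is none to reproduce. The check has two parts.

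**1. What each planned check can deliver for the cis-plus-trans instrument**

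| Check | What it does | Estimate that tolerates directional pleiotropy? |
|---|---|---|
| Cochran's Q and visual comparison | Flags SNP results that disagree | No |
| Leave-one-out | Shows reliance on single SNPs; worded for the primary analysis; same IVW estimator | No |
| Colocalisation | Separates a shared variant from two variants in LD; one variant acting by two routes would still colocalise | No |
| Phenome-wide look-up | Lists other associated traits; vertical and horizontal pleiotropy not separated | No |

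**2. An illustration of bias and of the power to notice it**

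Inputs from the document: events 7769 (breast) and 1149 (melanoma), table 2; R² of 4.17% for the lead cis SNP for PD-L1, Power section.

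Assumptions, not in the document: the true effect is null; the cis SNP is valid; every trans SNP has a pleiotropic ratio effect of HR 1.3; trans SNPs carry a share s of 30% or 70% of the IVW weight; there are five trans SNPs, so Q has 5 degrees of freedom.

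*Bias of IVW.* Log HR bias = s × ln(1.3), with ln(1.3) = 0.262.
- s = 0.3: exp(0.3 × 0.262) = 1.08
- s = 0.7: exp(0.7 × 0.262) = 1.20

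*Cis-versus-trans contrast.* Cis information I_c = events × R². Trans information I_t = I_c × s/(1 − s). SE of the difference = √(1/I_c + 1/I_t). z = 0.262/SE. The non-centrality of Q is z².

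| Site | s | I_c | I_t | SE of difference | z | Power of Q (5 df) | Power of direct contrast (two-sided 5%) |
|---|---|---|---|---|---|---|---|
| Breast | 0.3 | 324.0 | 138.8 | 0.101 | 2.6 | 48% | 73% |
| Breast | 0.7 | 324.0 | 755.9 | 0.066 | 4.0 | 88% | 98% |
| Melanoma | 0.3 | 47.9 | 20.5 | 0.264 | 1.0 | 10% | 17% |
| Melanoma | 0.7 | 47.9 | 111.8 | 0.173 | 1.5 | 18% | 33% |

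So Q is a useful alarm where events are many and a weak one where they are few. In this set-up the single contrast of trans against cis is more sensitive than Q at both sites, because it uses one degree of freedom, but it too has little power in melanoma.

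*A second illustration by simulation* (2000 runs per scenario). The assumptions are a true null; one cis SNP with R² 4.17%; 20 or 50 trans SNPs of R² 0.1% each; and 30% or 50% of trans SNPs with a direct effect of 0.02 log HR per SD of genotype, all in the same direction. Mean IVW estimates were HR 1.06 to 1.11 with 20 trans SNPs and 1.11 to 1.19 with 50. Q rejected in 64% to 99% of runs at 7769 events and 11% to 20% at 1149. The pattern is the same; the sizes again follow from the assumptions.

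**The case against.** Several points on the other side carry weight.

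- **The cis-only analysis already takes precedence.** It is the main analysis, and no decision rule in the article rests on the cis-plus-trans result. This stands and limits the importance of the point.
- **The plan does check for pleiotropy.** The look-up covers the instruments in general, and colocalisation is tied to significant MR results without being confined to cis loci. A reader might infer that trans loci are left unchecked; the text does not support that. What remains is that these are diagnostics, not estimates.
- **Q is not blind here.** A reader might infer that Q would miss the problem. Q misses a bias shared by all variants, but a valid cis SNP beside biased trans SNPs is heterogeneity, and in breast cancer Q has material power. The weakness is confined to sites with few events. In melanoma, moreover, the detectable PD-L1 HR in table 3 is 1.50, well above the illustrated bias.
- **The plan does not itself say that trans variants are more prone to pleiotropy.** It gives pleiotropy as the reason for restricting to cis; the converse is an inference, though a close one.
- **Not all pleiotropy biases IVW.** Vertical pleiotropy does not breach the assumptions, and balanced horizontal pleiotropy mainly widens the interval. The point concerns directional horizontal pleiotropy only.
- **Robust estimators can fail too.** The weighted median needs at least half the weight on valid SNPs, which fails at s = 0.7. MR-Egger needs pleiotropy to be unrelated to instrument strength (InSIDE), which fails if it acts as a common ratio effect. The fix is ordered accordingly.
- **An article may leave extra estimators to a fuller plan.** That is fair for detail. Here, however, the article states one estimator rule for all multi-SNP instruments and specifies its sensitivity analyses down to window sizes and LD cut-offs, so the rule as written can be assessed.

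**Conclusion.** The point holds in a limited form. IVW is the only estimator stated for multi-SNP instruments, and it carries over unchanged to cis-plus-trans instruments that lack the protection the main analysis relies on. None of the planned checks supplies an estimate that is valid under directional horizontal pleiotropy, and Q is weak where events are few.

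The size of any bias cannot be derived from the document. The HR 1.08 to 1.20 range rests wholly on the assumed trans weight and pleiotropic effect and is not a prediction. It is tempting to set it beside the detectable PD-L1 HR of 1.17 in breast cancer (table 3), but that figure was calculated around the lead cis SNP and is not a benchmark for a cis-plus-trans instrument. A reader might also infer that the two sets of results could not be interpreted together at all. That goes too far, since disagreement can be read as possible pleiotropy with the cis-only result retained. This is a worthwhile, low-cost improvement to a secondary analysis; it does not threaten the main conclusions.

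**What to change.** For cis-plus-trans instruments (r² < 0.001), prespecify beside IVW:

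1. The trans-only estimate against the cis-only estimate, with a test of their difference, as the leading comparison.
2. Where SNP numbers allow, the weighted median and MR-Egger with its intercept test, each with its assumption stated (at least 50% of the weight on valid SNPs; InSIDE).
3. A reading rule: disagreement is treated as possible pleiotropy and the cis-only result is retained. At sites with few events, a non-significant difference is not taken as evidence that pleiotropy is absent.

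Study status reports that analyses have begun, so the rule should be fixed and dated before the cis-plus-trans results are interpreted.

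Cost: a few more estimates on the same harmonised data and no new data. MR-Egger will be imprecise with few SNPs, and the trans-against-cis test will have low power at the smaller sites.
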